**Methods and design:**

This will be a parallel-group randomized, patient- and assessor-blinded trial. The study will recruit 60 ID patients assigned to a real mPFC-rTMS group or a sham mPFC-rTMS group. The allocation ratio is 1:1, with 30 subjects in each group. Interventions will be administered five times per week over a 4-week period, with an 8-week follow-up period. All participants will undergo neuropsychological and fMRI evaluations. The primary outcome measure of this study is the change scores of the Pittsburgh Sleep Quality Index (PSQI). The secondary outcome measures include the fMRI measurements, the Hamilton Depression Scale (HAMD), the Hamilton Anxiety Scale (HAMA), a sleep diary, and a polysomnography. Assessment of all parameters will be performed at baseline, post-treatment, and during follow-up.

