Two recent neuroimaging studies used functional magnetic resonance imaging (fMRI) to analyze the resting state functional connection (RSFC) of NAc in ID patients and revealed abnormal RSFC between NAc and mPFC which suggest the brain related to the severity of insomnia [16, 17]. Shao et al. [16] proposed an abnormal NAC-mPFC circuit in ID. In addition, the hypothalamus, a central role in sleep-wake regulation, was recently used as the seed for functional connection by fMRI, and the results showed that the bilateral hypothalamus and bilateral mPFC resting state functional connection were enhanced in ID patients and were positively correlated with sleep quality [18]. Moreover, neuroimaging revealed reduced gray matter density [19, 20], abnormal regional homogeneity (ReHo) [21], amplitude of low-frequency fluctuations (ALFF) [22], and reduced activation of mPFC [23, 24]. These studies suggest that mPFC may play an important role in the pathophysiological mechanism of insomnia.

Therefore, we hypothesized that 1-Hz rTMS stimulation over mPFC would improve insomnia symptoms of ID patients by altering mPFC seed functional connectivity in the group receiving real mPFC-rTMS group compared with the sham mPFC-rTMS group.

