#### Functional MRI scanning procedure

The resting-state fMRI data will be obtained at Zhenjiang Mental Health Center with a Philips 3.0-T MRI scanner. All fMRI images will be acquired from a gradient echo-echo plane imaging under the following parameters: 30 slices, repetition time (TR) = 2000 ms, echo time (TE) = 30 ms, thickness = 5 mm, field of view (FOV) =240 × 240 mm, flip angle = 90°, matrix size 64 mm × 64 mm, and total 185 volumes. Participants will be required to stay awake, keep their eyes closed, not move, close their eyes, and not try to think about anything. The real and sham mPFC-rTMS groups will be examined three times (baseline, post-treatment, and follow-up).

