### Statistical analysis

For clinical data, statistical analyses will be analyzed using Statistical Package for the Social Sciences (version 19.0). Two-sided tests will be considered statistically significant if *P* ≤ 0.05. Cases of any missing data should be listed and the reasons should be indicated. The main efficacy analyses will be conducted based on the intention-to-treat principle. Sociodemographic information and outcome indicator will be presented with the mean ± standard deviation or the frequency (%) for the real mPFC-rTMS group and the sham mPFC-rTMS group. Independent *t* tests will be used to compare the outcome indicators between the two groups before and after mPFC-rTMS. Paired *t* tests will be used to compare the pre-rTMS and post-rTMS outcome indicators within each group. A repeated measures analysis of variance with adjustments for non-sphericity will be applied to analyze the group differences and time-dependent effects of rTMS on outcome indicators.

For fMRI data, statistical analyses will use SPM12 (http://www.fil.ion.ucl.ac.uk/spm), Data Processing & Analysis of Brain Imaging toolbox (http://rfmri.org/dpabi), and VBM8 toolbox (http://dbm.neuro.unijena.de/vbm) plugged into MATLAB_R2018a (Mathworks, Inc., Natick, MA, USA). Original data will be preprocessed: slice timing, affine head motion, nonbrain extraction, spatial smoothing, and temporal filtering will be applied. The regional resting-state fMRI time series will extract for the bilateral mPFC by using the average functional time series of all voxels within each region. Significance was set at a *P* value < 0.05 after correcting for multiple comparisons using false discovery rate (FDR) correction. Pearson correlation will be used to investigate the RSFC between bilateral mPFC and the whole-brain regions, and then a Fisher’s *r*-to-*z* transform is employed. mPFC-based functional connectivity pre-rTMS and post-rTMS between the real and sham mPFC-rTMS group will be compared using independent *t* tests. Paired *t* tests will be used to compare pre-rTMS and post-rTMS mPFC-seed functional connectivity within each group.

There will be no interim analysis.

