## Discussion

Previous studies have shown that rTMS is effective in the treatment of insomnia, but no study selected targets based on neural network connectivity. We review the literature and find that mPFC may be one of the potential targets. Therefore, it is necessary to carry out further clinical trials to clarify the efficacy and possible neural mechanisms of mPFC-rTMS for ID patients. It is expected that this clinical trial will provide important data on the effect of rTMS and its possible neural mechanisms for ID.

We speculate that this effect may have relevance to the modulation mPFC-based functional connectivity. If our hypothesis is correct, functional connectivity maps of the sleep-related regions will be more modulated in the group receiving real mPFC-rTMS than in the sham mPFC-rTMS group. These results will provide insight into the potential mechanism of rTMS for ID.

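### The fMRI plan names no direct or baseline-adjusted test of whether connectivity changes more under real than sham rTMS; only the unadjusted post-rTMS comparison bears on that hypothesis

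*Protocol article*

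**What the plan says.** The mechanistic hypothesis appears twice in the protocol article. The Introduction expects real rTMS to improve insomnia "by altering mPFC seed functional connectivity in the group receiving real mPFC-rTMS group compared with the sham mPFC-rTMS group". The Discussion expects that connectivity maps of sleep-related regions "will be more modulated in the group receiving real mPFC-rTMS than in the sham mPFC-rTMS group". Both are real-versus-sham statements about change, and they serve the second of the two study objectives.

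The fMRI paragraph of Statistical analysis names two families of tests:

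- Between groups: "mPFC-based functional connectivity pre-rTMS and post-rTMS between the real and sham mPFC-rTMS group will be compared using independent" t tests.
- Within groups: paired "tests will be used to compare pre-rTMS and post-rTMS mPFC-seed functional connectivity within each group".

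A repeated measures analysis of variance is also planned. It "will be applied to analyze the group differences and time-dependent effects of rTMS on outcome indicators", but it stands in the preceding paragraph, which opens "For clinical data, statistical analyses will be analyzed using Statistical Package for the Social Sciences". The fMRI paragraph has its own software and threshold (P < 0.05, FDR-corrected), and it does not repeat the ANOVA.

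On the scans, Functional MRI scanning procedure states: "The real and sham mPFC-rTMS groups will be examined three times (baseline, post-treatment, and follow-up". The fMRI tests refer only to pre-rTMS and post-rTMS. The abstract gives fMRI its rank: "The secondary outcome measures include the fMRI measurements". The Sample size section treats the imaging part as exploratory and gives no calculation for it.

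**The concern.** More modulation in real than in sham is a statement about a difference between groups in change. The fMRI paragraph yields four kinds of map: real versus sham before treatment, real versus sham after treatment, pre versus post in real, and pre versus post in sham. None is the between-group difference in change, and none uses baseline connectivity to adjust the post-treatment comparison.

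Two things are at stake. First, the one map that bears on the hypothesis, real versus sham after treatment, discards the baseline scan. It gives up power and is exposed to chance baseline differences in a trial of 30 per group. Second, the plan does not say which map decides the question. The paired maps invite a reader to set a significant change in real beside a non-significant change in sham and take the contrast as evidence of a difference, which it is not. The article gives some reason to expect movement in both arms, at least on symptoms: the Introduction cites a significant placebo effect of sham stimulation, and PSQI in the pilot control group fell by 1.30.

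**Working it through.** The article gives no computed figure for fMRI, so there is nothing of its own to reproduce. The check sets each planned test against the hypothesis and then sizes the consequences for a single connection at uncorrected two-sided alpha 0.05. FDR correction over the whole brain would change the absolute figures.

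**Inputs.** From the Sample size section: 26 per group required, 30 recruited, 15% dropout. Then 30 × (1 − 0.15) = 25.5, so about 25 or 26 per group are scanned at the end. Randomisation is 1:1. Assumed, because the article does not give them: a standardised post-treatment difference of 0.5 or 0.8, a pre-post correlation r of 0.3, 0.5 or 0.7, and a common paired effect size d of 0.3 to 0.5.

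**Step 1. Which tests bear on the hypothesis.**

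- Real versus sham, pre: no. Before treatment any difference is due to chance.
- Real versus sham, post: yes. Randomisation makes expected baseline connectivity equal, so the post-treatment null is the same as the null of no difference in change. Simulated size with no treatment effect, 26 per group and r = 0.5, is 0.049.
- Pre versus post, in real or in sham: no. Each asks whether one arm changed.

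**Step 2. Side-by-side paired tests when both arms change equally.** If each paired test has power p, the chance of significance in real only is p(1 − p), and of disagreement either way 2p(1 − p). With 25 per arm:

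| paired d | p | real only | either way |
|---|---|---|---|
| 0.3 | 0.30 | 0.21 | 0.42 |
| 0.4 | 0.48 | 0.25 | 0.50 |
| 0.5 | 0.67 | 0.22 | 0.44 |

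At 26 per arm the ranges are almost the same: 21% to 25% and 43% to 50%.

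**Step 3. Power of three between-group tests, 26 per group.** For a post-treatment difference δ in SD units, the effective effect size is δ for the post-only test, δ/√(2(1 − r)) for the unadjusted change score (equivalent to group × time with two time points), and about δ/√(1 − r²) for baseline-adjusted ANCOVA. Power from the noncentral t distribution:

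| δ | r | post-only | change score | ANCOVA |
|---|---|---|---|---|
| 0.8 | 0.3 | 0.81 | 0.67 | 0.84 |
| 0.8 | 0.5 | 0.81 | 0.81 | 0.90 |
| 0.8 | 0.7 | 0.81 | 0.96 | 0.98 |
| 0.5 | 0.3 | 0.42 | 0.32 | 0.46 |
| 0.5 | 0.5 | 0.42 | 0.42 | 0.53 |
| 0.5 | 0.7 | 0.42 | 0.63 | 0.70 |

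ANCOVA has the most power in every row. The unadjusted change score falls below the planned post-only test when r < 0.5, because then 2(1 − r) > 1.

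**Step 4. Chance baseline imbalance.** The standard error of a standardised group difference is √(2/26) = 0.277. A baseline difference beyond 0.5 SD in a given connection corresponds to |z| > 0.5/0.277 = 1.80, a probability of about 7%. With a baseline difference of 0.5 SD and no treatment effect, the post-treatment difference has mean 0.5r and SD 0.277√(1 − r²), and the test rejects beyond about 1.96 × 0.277 = 0.54. For r = 0.5 (mean 0.25, SD 0.240) the rejection rate is about 11%. For r = 0.7 (mean 0.35, SD 0.198) it is about 16%. These rates are conditional on the imbalance; averaged over all randomisations the size remains 5%.

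**The case against.** The strongest reply is that the plan already holds a valid test. The post-rTMS real-versus-sham comparison has correct size under randomisation, and session, expectation and regression effects common to both arms cancel in it. This stands. A reader might infer that nothing planned addresses the hypothesis, or that the second objective cannot be answered validly. The documents do not support either inference.

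A second reply is that the 21% to 25% describes a rule of inference the article never states. This also stands: the article frames its hypothesis as real compared with sham and lists the between-group test first. The figure shows why the paired maps should not carry the inference; it is not an error rate of the plan as written.

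A third is that the wording may already cover change. The between-group sentence could loosely mean a comparison of pre-to-post change, and the outcome indicators in the ANOVA sentence could be stretched to fMRI because the abstract lists fMRI as a secondary outcome. Neither reading is secure. The parallel clinical sentence compares the groups before and after treatment, which points to two cross-sectional tests, and the ANOVA belongs to the paragraph on clinical data. Even if the ANOVA did extend to fMRI, an unadjusted group × time test need not improve on the post-only comparison.

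Finally, an article may leave detail to a fuller plan. That is fair for the 8-week scan, whose missing contrast is not an error in itself. It is weaker for the main fMRI test, because the article does list its fMRI tests and the list does not match the stated hypothesis.

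**Conclusion.** The point holds in limited form. The fMRI paragraph names no direct or baseline-adjusted test of the between-group difference in connectivity change. Only the unadjusted post-rTMS t test bears on the hypothesis. It is valid but inefficient, and for any single connection it is open to chance baseline imbalance. The pre-rTMS comparison and the paired tests do not test the hypothesis.

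The gain from adjustment runs from small to material: 0.03 to 0.17 in power at a 0.8 SD difference, and 0.04 to 0.28 at 0.5 SD. It depends on a pre-post correlation that the article does not give. All figures rest on the assumed effect sizes and correlations and on a single uncorrected test. The outcome is secondary and exploratory, so this is a low-cost improvement to the second objective and no threat to the trial's main result.

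**What to change.** In the fMRI paragraph of Statistical analysis, name one deciding test: an FDR-corrected between-group comparison of post-treatment Fisher-z connectivity with baseline connectivity as covariate. Change maps with the same covariate give the same group effect. Prefer this to an unadjusted change-score or group × time test, which can have less power than the test now planned when the pre-post correlation is below 0.5. Apply the same model to the 8-week scan. Label the within-group paired maps and the pre-rTMS comparison descriptive, and state that no real-versus-sham conclusion will be drawn from them.

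The cost is wording, settled before the imaging data are analysed. No extra scans or patients are needed. Because the baseline covariate takes a different value at each voxel or region, the sponsor should confirm that the chosen toolbox fits a covariate of that kind.

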## Discussion

Previous studies have shown that rTMS is effective in the treatment of insomnia, but no study selected targets based on neural network connectivity. We review the literature and find that mPFC may be one of the potential targets. Therefore, it is necessary to carry out further clinical trials to clarify the efficacy and possible neural mechanisms of mPFC-rTMS for ID patients. It is expected that this clinical trial will provide important data on the effect of rTMS and its possible neural mechanisms for ID.

We speculate that this effect may have relevance to the modulation mPFC-based functional connectivity. If our hypothesis is correct, functional connectivity maps of the sleep-related regions will be more modulated in the group receiving real mPFC-rTMS than in the sham mPFC-rTMS group. These results will provide insight into the potential mechanism of rTMS for ID.

## Trial status

The protocol version number is 1.1, and the date is 11 January 2020. The ethics committee of Zhenjiang Mental Health Center approved the study protocol on 3 January 2022 (permission 202007). This trial was registered on 10 December 2021 (ChiCTR2100054154). The trial started on 1 March 2022. The trial is currently recruiting participants. We predict that recruitment will be completed by 28 February 2023.

## Data Availability

All study-related data will be stored securely at the Zhenjiang Mental Health Center. The datasets analyzed during the current study are available from the corresponding author for future secondary analysis.
